## Study design - overview

The FLEX Study is a cluster randomized controlled trial. Participating schools were clustered by location within the state and school district. Schools within each district were randomly assigned to receive a school-based PA intervention (*100 Mile Club* or *Just Move*) or assigned to be a control school. Third and fourth grade students were enrolled and are being followed for two school years (Fig. 1). Data are collected at three time points: baseline (fall, school year 1), short-term (spring, school year 1; 5–6 months post-baseline) and long-term post-intervention (spring, school year 2; ≈1.5 years post-baseline). The study occurred in two waves, the first beginning during the 2014–2015 school year (*n* = 6 schools) and the second wave during the 2015–2016 (*n* = 18 schools) school-year. Due to unforeseen weather circumstances and school cancellations in Winter 2015, additional student participant recruitment beyond the initial six schools was put on hold until the following school year. The investigative team determined that these schools would be designated as Wave 1. Approval for the study was obtained from the Tufts University IRB (Medford, MA) and additionally from individual school districts where required.

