Briefly, child-level data collection takes place at each participating school during regular school hours at each of the three time points (baseline, midpoint, and post-intervention). Exceptions are demographic data, which are collected once at baseline, and fitness measurements, which are conducted at a separate time once per school year. Child-level standardized test scores for Math and English Language Arts (ELA) are collected from the Massachusetts Department of Elementary and Secondary Education (DESE) after testing is completed each spring. School-level data is collected once per year (physical activity environment and food environment surveys, along with attendance data). Trained research assistants (RAs) and study staff administer all instruments and assessments according to the written study protocol. At baseline, there were 174 participants enrolled from Wave 1 schools and 1008 from Wave 2 schools. Baseline measurements were conducted in the fall/early winter of Year 1 (Wave 1 – February-March, 2015; Wave 2 – September 2015-February 2016). Short-term measurements were conducted at the end of the first school year (Wave 1 – May-June 2015; Wave 2 – April-June 2016) and post-intervention measurements will be conducted approximately 18 months after baseline at the end of the second school year (Wave 1 – March-April 2016; Wave 2 – April-June 2017). At time of enrollment, participants are assigned a unique 5-digit code which is used in place of name or other identifiers to link participant to all their study data. The study project manager maintains an electronic, password-protected list linking participant with their unique ID.

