## Sample size calculation and data analyses

A priori sample size calculations for the FLEX study were based on several recent school-based physical activity interventions. Power calculations for our analysis with respect to school-time MVPA were based on the findings of Verstraete et al. [51]. In this study, the intervention group showed a greater percentage of recess time spent in MVPA, compared to controls (mean ± SD: 53.4 ± 25.6 vs. 43.5 ± 27.6). While we expect a larger difference from our more intensive intervention, we used this conservative estimate to calculate our sample size, resulting in an estimated sample size of 115 participants per arm (total *n* = 345) with power of 80 %. For total daily MVPA, we referred to the findings from a RCT to increase PA through curriculum modification by Donnelly et. al [52]. In this study, the intervention group received 90-min/week of physically active classroom lessons (≈10 min/lesson) which resulted in an increase of 26 min of weekly MVPA in the intervention group compared to controls (within group SDs = 40). We estimated that a sample size of 39 per arm (117 total) is needed to detect differences of this magnitude. Thus, the sample size of 345 will be sufficient. Because the number of clusters is fixed at 21 schools, 7 per arm, we used a protocol suggested by Hemming et al. [53] to adjust for the clustering. Assuming an ICC of 0.03 and attrition rate of 25 % per year, we arrived at a final sample size of 903 students, 43 per school.

During the 2014–2015 study roll out, Boston experienced a severe snow season which impacted the school recruitment process. After consulting with the funding agency we subsequently extended school recruitment and intervention implementation into the next year, creating the two-wave structure described previously.

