For statistical analyses, descriptive statistics for variables of interest will be compiled and tabulated. To test the effect of school-based PA programs on minutes spent in MVPA, we will compare *100 Mile Club* vs. control and *Just Move* vs. control as separate tests using mixed effects models. Outcomes of interest are changes in minutes of MVPA between midpoint vs. baseline and post-intervention vs. baseline. The key regression coefficient of interest is the intervention by time interaction term, which will indicate if the intervention is associated with a significant higher/lower change in MVPA across time compared to the control. The unique school identification number will be modeled as random intercepts to adjust for clustering. We will examine both unadjusted and adjusted (including covariates such as sex, race/ethnicity, weight status) regression coefficients of the respective program and conclude if the difference in MVPA minutes is statistically significant. A similar approach will be used to examine the impact of PA programming on academic/cognitive outcomes. All analyses will be performed using SAS 9.3 (Cary, NC, USA) and results with p-values less than 0.05 will be considered statistically significant.

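### The 903-student figure allows for one year of the stated 25 % per year attrition, so in the planned 21 schools it gives about 75 to 78 % power, not 80 %, for long-term school-time MVPA

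*Protocol article*

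**What the plan says.** Under Sample size calculation and data analyses, the protocol article takes school-time MVPA from an earlier trial of recess activity ("53.4 ± 25.6 vs. 43.5 ± 27.6", mean ± SD), "resulting in an estimated sample size of 115 participants per arm" "with power of 80" %. A second calculation, for total daily MVPA, needs only 39 per arm, so the school-time figure governs. The article then allows for clustering: "Because the number of clusters is fixed at 21 schools, 7 per arm". With an ICC of 0.03 and attrition of 25 % "per year, we arrived at a final sample size of 903 students, 43 per school".

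Study design - overview says: "Third and fourth grade students were enrolled and are being followed for two school years". It places the midpoint 5–6 months after baseline and the last measurement about 1.5 years after baseline. The analysis paragraph names two MVPA changes of interest, midpoint against baseline and post-intervention against baseline. The sample size text does not say which of them the 903 is meant for.

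On enrolment, the Overview under Data collection methods reports: "At baseline, there were 174 participants enrolled from Wave 1 schools and 1008 from Wave 2 schools". The Schools section gives 24 schools, 6 in Wave 1 and 18 in Wave 2.

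**The concern.** Attrition is given as an annual rate and the follow-up spans two school years, so a reader expects the inflation to compound over that period. If it was applied once, 43 per school leaves fewer analysable children at the long-term visit than the clustering formula requires, and the 80 % does not carry over to that contrast.

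The long-term change is one of only two MVPA changes tested, and school-time MVPA is part of the primary aim. Because the article names no time point, a reader will take the 903 and the 80 % to apply to both changes. What is at stake is whether the published justification is accurate for the later one.

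**Working it through.** **Inputs** (all from Sample size calculation and data analyses unless noted): difference 53.4 − 43.5 = 9.9; SDs 25.6 and 27.6; power 80 %; 7 schools per arm; ICC 0.03; attrition 25 % per year. The significance rule is "p-values less than 0.05 will be considered statistically significant". Sidedness is not stated; two-sided is assumed here because it reproduces the 115.

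**Step 1, before clustering.** Mean variance = (25.6² + 27.6²)/2 = 708.56, SD 26.62. Then n = 2 × 708.56 × (1.96 + 0.8416)² / 9.9² = 113.5 per arm by the normal approximation. The t-test version gives 114.45, rounded up to 115. The article's 115 is reproduced.

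**Step 2, fixed number of clusters.** m = n(1 − ICC)/(k − n × ICC) = 115 × 0.97/(7 − 3.45) = 31.4, so 32 analysable children per school.

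**Step 3, attrition.** 32/0.75 = 42.7, so 43 per school, and 43 × 21 = 903. Both published figures are reproduced with a single 25 % loss. None of the longer-loss variants tried gives 43:

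| Loss allowed for | Retained | Per school | 21 schools |
|---|---|---|---|
| one year | 0.75 | 43 | 903 |
| 1.5 years, 0.75^1.5 | 0.650 | 50 | 1,050 |
| two years, 0.75² | 0.5625 | 57 | 1,197 |
| two years, additive | 0.50 | 64 | 1,344 |

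Against 903, 1,050 is 16 % more and 1,197 is 33 % more.

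**Step 4, power of 43 per school for school-time MVPA.** Effective n per arm = 7m/(1 + (m − 1) × 0.03), where m is the number retained per school; power by normal approximation, two-sided 0.05.

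| Loss | m | Design effect | Effective n per arm | Power |
|---|---|---|---|---|
| one year | 32.25 | 1.94 | 116.5 | 81.0 % |
| 1.5 years | 27.9 | 1.81 | 108.1 | 78.1 % |
| two years | 24.2 | 1.70 | 99.9 | 74.8 % |
| additive 50 % | 21.5 | 1.62 | 93.2 | 71.9 % |

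**Step 5, total daily MVPA.** With a difference of 26, SD 40 and effective n 99.9 (two years of loss), power is 99.6 %.

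**Step 6, the realised design.** Wave 1: 174/6 = 29 per school. Wave 2: 1,008/18 = 56 per school. Total 1,182 children in 24 schools. Assume 2 Wave 1 and 6 Wave 2 schools per arm (the article does not give the split), and sum each school's effective n:

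- 1.5 years: 2 × 12.27 + 6 × 17.65 = 130.4, power 85.2 %.
- Two years: 2 × 11.18 + 6 × 16.45 = 121.0, power 82.5 %.
- Additive 50 % loss: 2 × 10.32 + 6 × 15.47 = 113.5, power 80.0 %.

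**The case against.** The strongest reply is that the trial as run is adequately powered by its own criterion, and that stands. With 8 schools per arm the formula in Step 2 gives 115 × 0.97/(8 − 3.45) = 24.5, so 25 analysable children per school. With two years of loss, 25/0.5625 = 44.4, so 45 per school and 45 × 24 = 1,080 in all. Enrolment was 1,182. A reader might infer from the 21-school shortfall that a null long-term result would come from an underpowered comparison; the realised figures do not support that.

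Other parts of the reply also stand:

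- Two full years of loss is the harsher reading. The last visit is at about 18 months, and pro-rating gives 78.1 %, close to target. The 75 % is one end of a range and should not be presented as the answer.
- Only school-time MVPA is touched. It would be wrong to say that the planning figures fail for long-term MVPA in general.
- The article attaches 80 % to the 115 per arm before clustering and names no time point. At 5–6 months a full year's loss is a generous allowance.
- The difference between 21 planned and 24 realised schools might be read as a second error. It is not: the calculation is labelled a priori, and the article explains the extension of recruitment after the severe winter.

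What does not stand is that the sentence is therefore right. It gives an annual rate and a total that agree only over one year, and nothing in it limits the total to the midpoint. Nor is this detail left to a fuller document: the figures are printed and can be checked.

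**Conclusion.** The point holds as a correction of a stated planning figure. The 903 allows for one year of loss, while one of the two tested changes falls about 18 months after baseline. On the article's own inputs, 903 children in 21 schools give about 75 to 78 % power for long-term school-time MVPA, a shortfall of 2 to 5 percentage points, and 80 % would need 1,050 to 1,197 children.

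The conclusion goes no further than that. The midpoint and total daily MVPA are unaffected, and the enrolled sample restores about 82 to 85 % at the long-term visit (about 80 % if half the children are lost). Severity is moderate to minor.

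The figures rest on a two-sided 0.05 test, the normal approximation, an ICC of 0.03, the effect and SDs of the cited recess trial and, for the realised design, 2 Wave 1 and 6 Wave 2 schools per arm.

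**What to change.** In Sample size calculation and data analyses:

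1. State that 903 students (43 per school in 21 schools) allow for one year of 25 % loss only.
2. Give the long-term position for school-time MVPA as a range: about 75 to 78 % power at 903, or 1,050 to 1,197 children (50 to 57 per school) for 80 %, according to whether loss is counted over two years or 1.5.
3. Add that the 24 schools and 1,182 children enrolled give about 82 to 85 % power at the long-term visit on the same inputs, with the actual split of Wave 1 and Wave 2 schools by arm in place of the assumed 2 and 6.

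The cost is a short recalculation and two or three sentences. Enrolment, conduct and analysis do not change.

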**Methods:**

Twenty-four public elementary schools from low-income, ethnically diverse communities around Massachusetts were recruited and randomized to receive either *100 Mile Club®* (walking/running program) or *Just Move™* (classroom-based PA program) intervention, or control. Schoolchildren (grades 3–4, approximately 50 per school) were recruited to participate in evaluation. Primary outcome measures include PA via 7-day accelerometry (Actigraph GT3X+ and wGT3X-BT), cognitive assessments, and academic achievement via state standardized test scores. Additional measures include height and weight, surveys assessing psycho-social factors related to PA, and dietary intake. School-level surveys assess PA infrastructure and resources and intervention implementation. Data are collected at baseline, mid-point (5–6 months post-baseline), and post-intervention (approximately 1.5 years post-baseline). Demographic data were collected by parents/caregivers at baseline. Mixed-effect models will test the short- and long-term effects of both programs on minutes spent in MVPA, as well as secondary outcomes including cognitive and academic outcomes.

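### The 903-student target allows for one 25 % loss, although the text assumes 25 % per year and the long-term comparison falls in the second school year

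*Protocol article*

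**What the plan says.** All of the calculation is in the protocol article, section Sample size calculation and data analyses.

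- The effect on school-time MVPA is borrowed from an earlier school trial, in percent of recess time: "mean ± SD: 53.4 ± 25.6 vs. 43.5 ± 27.6". The individual-level result is given as "resulting in an estimated sample size of 115 participants per arm (total *n* = 345) with power of 80" %.
- Clustering: "Because the number of clusters is fixed at 21 schools, 7 per arm".
- Further assumptions: "Assuming an ICC of 0.03 and attrition rate of 25 % per year".
- Result: "we arrived at a final sample size of 903 students, 43 per school".

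The outcomes of interest in the same section are the changes from baseline to midpoint and from baseline to post-intervention. The study design overview follows children over two school years and places the last measurement about 1.5 years after baseline. The data collection overview says approximately 18 months.

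On the trial as recruited, the abstract says: "Twenty-four public elementary schools from low-income, ethnically diverse communities around Massachusetts were recruited and randomized". The data collection overview says: "At baseline, there were 174 participants enrolled from Wave 1 schools and 1008 from Wave 2 schools". The sample size section calls its calculation a priori and then explains why recruitment was extended into a second wave. It does not redo the calculation for the larger number of schools.

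**The concern.** An annual loss of 25 % and follow-up into a second school year imply more than one 25 % loss by the last measurement. If the target covers only one, the stated 80 % power does not apply to the long-term comparison, which is one of the two comparisons the analysis is built on. Either the attrition assumption or the number of children is misstated, and the reader cannot tell which.

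The calculation also describes 21 schools, whereas 24 were randomised. The article therefore gives no power or detectable difference for the trial that was recruited, and a null long-term result could not be set against a correct figure.

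**Working it through.** **Inputs.** From the sample size section: means 53.4 and 43.5, SDs 25.6 and 27.6, power 80 %, k = 7 schools per arm, ICC ρ = 0.03, attrition 25 % per year, significance level 0.05. From the abstract and the data collection overview: 24 schools and 174 + 1008 = 1182 children. Assumed: two-sided testing, and 24/3 = 8 schools per arm.

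**1. Individual-level size.** Pooled SD = √((25.6² + 27.6²)/2) = 26.62. Standardised difference d = 9.9/26.62 = 0.372. The normal formula 2(1.960 + 0.842)²/d² gives 113.5, so 114 per arm. The t-based version gives 115, as stated.

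**2. Fixed number of schools.** Completers per school m = n(1 − ρ)/(k − nρ) = 115 × 0.97/(7 − 3.45) = 31.4, so 32.

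**3. Attrition.** One 25 % loss: 32/0.75 = 42.7, so 43, and 43 × 21 = 903. The published figure is reproduced exactly.

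**4. The same chain with the attrition as worded.**

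| Loss by post-intervention | Retained | Per school | Total (21 schools) |
|---|---|---|---|
| 25 % once | 0.75 | 43 | 903 |
| 25 % per year, 1.5 years | 0.75^1.5 = 0.650 | 50 | 1050 |
| 25 % per year, 2 years compounded | 0.75² = 0.5625 | 57 | 1197 |
| 25 % twice, added | 0.50 | 64 | 1344 |

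No reading with more than one year of loss gives 903.

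**5. Power of 43 per school in 21 schools.** Effective n per arm = k·m/(1 + (m − 1)ρ). Power = Φ(d√(n/2) − 1.960).

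| Loss | m retained | Design effect | Effective n per arm | Power |
|---|---|---|---|---|
| 25 % once | 32.25 | 1.938 | 116.5 | 81.0 % |
| 1.5 years | 27.93 | 1.808 | 108.1 | 78.1 % |
| 2 years compounded | 24.19 | 1.696 | 99.9 | 74.8 % |
| 50 % | 21.5 | 1.615 | 93.2 | 71.9 % |

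The first row also serves for the midpoint. That measurement is 5–6 months after baseline, so one full 25 % loss is a cautious allowance.

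**6. The trial as recruited.** 1182/24 = 49.25 per school, 8 schools per arm, same formulas.

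| Loss | m retained | Effective n per arm | Power |
|---|---|---|---|
| 1.5 years | 31.99 | 132.6 | 85.7 % |
| 2 years compounded | 27.70 | 123.1 | 83.1 % |
| 50 % | 24.62 | 115.3 | 80.6 % |

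School sizes differ by wave: 174/6 = 29 in Wave 1 and 1008/18 = 56 in Wave 2. With two Wave 1 and six Wave 2 schools in each arm (an assumption), effective n after two compounded years is 120 to 121 and power is 82.1 to 82.5 %. At 50 % loss it is 79.7 to 80.0 %.

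The difference detectable with 80 % power is 2.80 × √(2/123.1) = 0.357 SD. On the borrowed scale that is 0.357 × 26.62 = 9.5 percentage points, against the assumed 9.9.

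**7. Sensitivity to the reference distribution.** With a t reference on between-school degrees of freedom (2k − 2), the recruited trial has about 77 % power after two compounded years (14 df), or 76 % with unequal wave sizes. On the same kind of basis (12 df), 903 with its single 25 % loss has 74 %.

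**The case against.** A reader might infer that the trial as run falls short of 80 % power, and that 21 versus 24 schools is part of the error. The documents do not support either inference.

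- The extra schools and children raise power. On the normal approximation, which is the basis on which 903 meets its stated power, the recruited trial stays above 80 % after two compounded years of loss.
- The figure of 76–77 % appears only after a change to t critical values on 14 df. On that kind of yardstick the protocol's own plan is already at 74 % with one loss, so most of the gap comes from the yardstick and not from the attrition slip. The article names no reference distribution for the clustered calculation and does not say whether each contrast comes from a two-arm or a three-arm model, so 14 df is not fixed by the text.
- The calculation is labelled a priori and the later extension is explained. The 21 is a planning figure left standing, not an arithmetic mistake.

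Two full years of loss is also the harsher reading. The design places the last measurement at about 1.5 years, and the Wave 1 dates (February–March 2015 to March–April 2016) span only about 13 months. At 1.5 years the planned design is short by about two percentage points.

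The effect size is in percent of recess time ("the intervention group showed a greater percentage of recess time spent in MVPA"), whereas the analysis is in minutes. The article openly uses it as a conservative stand-in, so this is secondary.

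All of these objections stand. None of them reconciles an annual 25 % with a target that contains 25 % once.

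**Conclusion.** The point holds for the stated plan. The 903 and the per-year attrition rate cannot both be right for the post-intervention comparison. On the stated inputs, 43 per school in 21 schools gives about 78 % power (1.5 years of loss) to 75 % (two years compounded), and reaching 80 % would take about 1050 to 1197 children. The midpoint comparison is unaffected, at about 81 %.

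For the trial as recruited, power on the protocol's own basis is about 82–83 % after two compounded years and about 86 % at 1.5 years. It is therefore not shown to fall short of 80 %. What is missing is a statement of this in place of the superseded figure.

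These results assume two-sided testing at 0.05, ICC 0.03, the borrowed effect and SDs, and 8 schools per arm. The article promises only comparable numbers of schools in each arm.

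**What to change.** 1. State whether 25 % is the loss per year or over the whole study. If overall, correct the wording, and 903 stands. If per year, correct the 903 (to 1050 or 1197, according to the period) or give the power that 903 provides at post-intervention.
2. Add the calculation for the trial as recruited: 24 schools with the actual number per arm, 1182 children, the unequal wave sizes, the attrition period used, and the resulting power and detectable difference at midpoint and post-intervention.
3. Name the reference distribution. If a t reference on between-school degrees of freedom is shown, present it as a sensitivity figure (about 76–77 % with 14 df after two compounded years), not as the correct value.

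This costs one recalculation and a rewritten paragraph. No further enrolment is needed, and no outcome, test or procedure changes.

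### The change-from-baseline contrast for MVPA is valid but uses the collected baseline inefficiently, and the stated 80 % power was not computed for it

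*Protocol article*

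**What the plan says.** The section on sample size and data analyses fixes the outcome: "Outcomes of interest are changes in minutes of MVPA between midpoint vs. baseline and post-intervention vs. baseline". It continues: "The key regression coefficient of interest is the intervention by time interaction term", which is to show "if the intervention is associated with a significant higher/lower change in MVPA across time compared to the control". Each programme is compared with control in its own mixed model, with a random intercept for school. Adjusted and unadjusted coefficients are both planned. The covariates given as examples are sex, race/ethnicity and weight status. Baseline MVPA is not among them, and nothing says that the arms share one baseline mean. The cognitive and academic outcomes are to be handled in a similar way.

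Table 1 shows accelerometry at baseline, midpoint and post-intervention, so the baseline value is available.

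The sample size for school-time MVPA rests on two group levels of recess time spent in MVPA ("mean ± SD: 53.4 ± 25.6 vs. 43.5 ± 27.6"), "resulting in an estimated sample size of 115 participants per arm" at 80 % power. No SD of change and no baseline-to-follow-up correlation is given for this outcome.

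**The concern.** Under randomisation, a difference in mean changes and a baseline-adjusted difference in follow-up means estimate the same effect. They differ in precision. The change score subtracts the whole baseline value, although only a fraction r of it predicts follow-up; adjustment subtracts the fraction that the data support. When r is low, subtracting all of the baseline adds more noise than it removes.

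Two things are at stake. One is precision given away in a trial with few schools per arm. The other is that the 80 % belongs to a different comparison from the one to be tested, so the power of the planned test is unknown from the article. A low r is conceivable: each measure is one 7-day wear period, Wave 2 baselines ran from September to February with follow-ups in April to June, and the last follow-up comes about 18 months after baseline.

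**Working it through.** **Inputs from the article.** Means 53.4 and 43.5, so the difference is 9.9; SDs 25.6 and 27.6; power 80 %; 7 schools per arm; ICC 0.03; attrition 25 % per year; 43 per school, 903 in total; enrolment 174 + 1008 = 1182 in 24 schools. The significance level is 0.05 ("results with p-values less than 0.05 will be considered statistically significant"), taken as two-sided because the text allows higher or lower change. **Assumed:** r, which the article does not give.

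**1. The plan's own figures.** Pooled SD = √((25.6² + 27.6²)/2) = 26.62; standardised difference 9.9/26.62 = 0.372. The t-test sample size is 114.45, so 115 per arm. Fixed clusters: 115 × 0.97/(7 − 115 × 0.03) = 111.55/3.55 = 31.4, so 32 completers per school; 32/0.75 = 42.7, so 43; 43 × 21 = 903. All figures reproduce, as a comparison of follow-up levels that makes no use of baseline.

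**2. Variance relative to that comparison.** Change: 2(1−r). Baseline-adjusted: 1−r². The ratio of adjusted to change is (1−r²)/(2(1−r)) = (1+r)/2, below 1 for every r < 1: 0.65 at r = 0.3, 0.75 at 0.5, 0.85 at 0.7.

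**3. Power in the planned design.** Design effect 1 + 31 × 0.03 = 1.93. Standard error for follow-up levels = 26.62 × √(2 × 1.93/224) = 3.494, giving 80.9 % power (normal approximation). Multiplying the variance by the factors in step 2:

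| r (school means) | Change | Baseline-adjusted |
|---|---|---|
| 0.2 | 61.0 % | 82.4 % |
| 0.3 | 66.8 % | 84.4 % |
| 0.4 | 73.4 % | 87.1 % |
| 0.5 | 80.9 % | 90.5 % |
| 0.6 | 88.6 % | 94.3 % |
| 0.7 | 95.5 % | 97.8 % |

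The change contrast reaches 80 % at r = 0.489.

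**4. What determines r.** For school means of m children, r = (m × ICC × C + (1−ICC) × S)/(1 + (m−1) × ICC), where C is the correlation over time of the school effect and S that of the child within school. With m = 32, r = (0.96C + 0.97S)/1.93. A school effect constant over time (C = 1) gives r = 0.497 even at S = 0. Power of the change contrast is then 80.7 % at S = 0, 88.5 % at S = 0.2 and 95.4 % at S = 0.4. With less stable schools it drops: 77.1 % at C = 0.5, S = 0.4; 70.0 % at C = 0.5, S = 0.2; 61.0 % at C = 0.2, S = 0.2.

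**5. Other numbers of completers.** Planned recruitment after two years of attrition leaves 43 × 0.75² = 24.2 per school. Actual enrolment is 1182/24 = 49.25 per school, so 36.9 after one year and 27.7 after two; 8 schools per arm is assumed.

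| Schools × completers per arm | Break-even r for 80 % | Change power, C = 1, S = 0 | Change power, C = 1, S = 0.2 |
|---|---|---|---|
| 7 × 32 | 0.49 | 80.7 % | 88.5 % |
| 7 × 24.2 | 0.56 | 69.0 % | 78.4 % |
| 8 × 36.9 | 0.37 | 90.1 % | 95.2 % |
| 8 × 27.7 | 0.46 | 80.3 % | 88.2 % |

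These calculations ignore the small-sample degrees of freedom and the cost of estimating the baseline slope from few schools. That cost weighs most where r is high and the gain from adjustment is already small.

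**The case against.** The strongest reply is that nothing here is an error. An intervention-by-time term in a mixed model is a valid analysis of a randomised trial. The covariate list is open-ended, and a longitudinal model with a common baseline mean also reads its effect from that interaction, so the article does not expressly rule out the better analysis. This stands as far as validity goes. It does not remove the point, because the outcome is stated as a change and neither adjustment for baseline nor a common baseline mean is stated.

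A reader might infer that the trial is underpowered. The documents do not support that. They give no r; a shortfall at 32 completers needs r below about 0.49, which does not arise if school effects are stable; and enrolment exceeded the planned 903. For total daily MVPA, sized at 39 per arm on 26 min with SD 40, 115 effective children per arm leave ample room. Taking 40 as the SD of a level, the change contrast at r = 0 has standard error 40 × √(2 × 2/115) = 7.46 and about 94 % power.

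A reader might also infer that baseline information is thrown away. It is used, but with the wrong weight.

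Finally, baseline imbalance arising from recruitment might seem to strengthen the case. Systematic imbalance would contradict a common baseline mean, and covariate adjustment would not automatically cure it. Randomisation in blocks stratified by district also limits chance imbalance. The point therefore rests on efficiency alone.

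**Conclusion.** The point holds as one of efficiency and of mismatch between sizing and analysis. In large samples the planned contrast is less precise than a baseline-adjusted one at every r < 1: adjustment brings the variance to 65–85 % of the change variance for r from 0.3 to 0.7. This does not depend on the ICC or the number of schools.

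The 80 % was obtained for follow-up levels of school-time MVPA. Whether the change contrast attains it depends on an r that is not given: below about 0.49 it does not, at the planned 7 × 32 completers per arm with ICC 0.03. A loss of power is thus possible but conditional, and stable school effects or the actual enrolment make it less likely. In that planned design the baseline-adjusted contrast never has less than 80.9 %.

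**What to change.** State in the analysis plan that midpoint and post-intervention MVPA are the outcomes of the mixed model, with the child's baseline MVPA and the school-mean baseline MVPA as covariates, and that the effect is the arm difference at each follow-up. A longitudinal model with a common baseline mean is an alternative, provided that baseline was measured before any intervention effect and the arms differ there only by chance. Use the same form for the cognitive outcomes. Say also that the 80 % refers to follow-up levels, or give power for the chosen contrast over a range of r.

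The cost is a few lines of SAS code and some wording. No new data are needed, and Wave 2 post-intervention measurements (April–June 2017) were still ahead when the article appeared, so the change could be fixed before the final data.
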